### Study setting

This is a multicentre study with “Encompass” implemented with parents and carers recruited from two NHS trusts in England serving urban areas with high levels of social deprivation and ethnic diversity. Local collaborators will be identified from each site.

The collaborators will be responsible for the local administration of the project by directly identifying potential participants from the clinical database and initiating the approach by providing the study information sheet to parents. They will also be involved in the recruitment of facilitators who will deliver the intervention.

We will access and recruit families in receipt of health and social care services at each participating NHS Trust, as well as professionals employed by both NHS trusts.

### Patient and public involvement

A patient and public involvement (PPI) group was formed during the initial phases of the study setup. The group consists of four mothers who live in the study areas, and all have a child with a complex neurodisability. The group met approximately every 3–4 months in the first year to build rapport, to discuss the study logistics and review any participant-facing documents and to co-adapt the manual and delivery plan for “Encompass”.

### Participants and recruitment

The study population are as follows:Parents/carers of children with a diagnosed and disclosed neurodisability (for example cerebral palsy), who reside in the study areasChildren of the above parents/carersFacilitators responsible for the delivery of the coadapted parent/carer group programme. The facilitator team will include a healthcare professional (likely physiotherapist or occupational therapist) and an “expert parent” with lived experience.Key NHS partners involved in the delivery and commissioning of health and care services, for example clinical managers, service leads or commissioners.

A SPIRIT diagram presents the planned flow of participants in Fig. 1 and the eligibility criteria in Table 1 below.

**Fig. 1 Fig1:**
[figure not shown]
Flow of participants. *Family Empowerment Scale (FES), Power Ladder Question (PLQ), Parent Patient Activation Measure (P-PAM), Warwick-Edinburgh Mental Wellbeing Scale (WEMWBS), EuroQoL-5D-5-level (EQ-5D-5L), †parent/carer greatest needs and goals, ‡intervention satisfaction survey

**Table 1 Tab1:** Inclusion and exclusion criteria

	Inclusion	Exclusion
Parents/ carers	Parents and carers who are as follows: • Care for a child (< 5 years at the time of enrolment) with a complex neurodisability^a^ • Have received a diagnosis for their child, which has been disclosed to them, even if this is a diagnosis such as SWAN (Syndrome Without A Name) • Reside in the boroughs of Newham or Tower Hamlets, East London • ≥ 18 years of age	• Have a child with a developmental disability where there are no functional physical impairments as part of their complex needs. For example, children diagnosed with autism spectrum disorder, attention-deficit hyperactivity disorder, and intellectual impairments will be excluded unless they have a functional physical impairment with a neurological cause too • Have a child with a progressive neurological condition such as Duchenne’s Muscular Dystrophy as the family’s needs would be different from those whose child has a life-long condition but is not progressive • Have a child with a structural physical impairment not caused by a neurological event or neurological difficulties. For example, children born with a limb difference or a child with hearing loss • Do not have capacity to consent • Do not meet the inclusion criteria as specified above • There are no exclusions based on language, as interpreting/translating services will be offered
Children	Children of the above parents/carers	The same above exclusion criteria regarding diagnosis apply
Facilitators	1. The health professional who facilitated the “Encompass” groups. The inclusion criteria for this facilitator were as follows: • Therapists or healthcare professionals who work with children with disabilities and who are open to learning with families about their children • Need to be registered with the Health and Care Professionals Council and should ideally have > 5-year post-graduate experience working with a paediatric population • Confident in working with children with complex neurodisability, such as cerebral palsy 2. The expert parent who facilitated the “Encompass” groups. The inclusion criteria for this facilitator were as follows: • Parents/carer of children with complex neurodisability who are identified through other services as potentially being able to facilitate a group as an “expert parent” • Prior experience in training or using participatory approaches — not essential	• Inability to read and speak English • Inability to commit to a 6-month period of work to the best of their knowledge
Key NHS partners	Staff from the NHS that are either involved in the delivery or commissioning of community child healthcare services in Newham or Tower Hamlets Examples include clinical managers, service leads or commissioners	

^a^Complex neurodisability for this study is based on need over a specific diagnosis. Children should have the following: A non-progressive neurological disorder either caused by a congenital brain abnormality or an acquired long-term condition caused by a neurological event (e.g. Hypoxic-Ischemic Encephalopathy or Traumatic Brain Injury), resulting in: A functional physical impairment and Additional difficulties with cognition, hearing and vision communication, emotion and behaviour can form part of the child’s clinical picture, but functional physical difficulties must be present

### Eligibility criteria

#### Recruitment

We will ensure recruitment of parents/carers of children with a known diagnosis of a complex neurodisability, such as cerebral palsy, with wide-ranging insights and experiences including clinical features, demographics (including family structure) and service use history. Potential participants will be approached by a known clinician and recruitment posters placed at NHS sites.

We will make concerted efforts to engage and recruit from those families who historically have been less engaged with clinical services (determined by the children and young people service use history). Participants in the Encompass 1 study were asked their opinions on how to reach more people for the intervention. Parents/carers and healthcare professionals gave suggestions which included the use of posters placed in libraries, general practice (GP) surgeries, schools or community groups. It was suggested that invitations should make it clear that interpretation services will be available.

We do anticipate some recruitment challenges which were explored in the Encompass 1 study. Parents with older children with complex neurodisability report that they would have liked to be invited to a programme such as “Encompass” in the early stages of their journey. However, there was acknowledgement that this can be an overwhelming time, and adding additional appointments to family’s schedules might be a barrier. This study will be important in exploring the feasibility of recruiting parents/carers into the programme, for example through recording reasons for non-participation.

#### Parents/carers of children with complex neurodisability 

The clinical team caring for the children with complex neurodisability will identify eligible cases and gain their consent from parents/carers to be contacted by the research team.

Parents/carers who are interested in taking part will be asked if they agree to being contacted by the research team. They will then email or phone potential participants to explain the study and provide them with a participant information sheet (PIS) and informed consent form. Potential participants will be invited to take time to read and review the study documents and have an opportunity to ask any questions. Informed consent will either be taken in person (via a signed hard copy form) or remotely (via a signed copy form).

Parents/carers who attend the group will have the option of an interpreter if required. Selected parents/carers will take part in semi-structured interviews after the programme, where their travel or data costs will be covered along with interpreter services.

#### Facilitators 

We aim to recruit a healthcare professional (such as a physiotherapist or occupational therapist) with appropriate experience of working with children with complex neurodisability, as well as an “expert parent” with lived experience to facilitate the group programme together.

The healthcare professional role will be advertised in community child health services in East London, and the expert parent role will be advertised through parent/carer form mailing lists as well as online support groups. The PPI group will provide further suggestions on different groups and charities to approach as well as any connections via their children’s schools or activities.

Facilitators will be paid for their time in line with NHS agenda for change pay scales [40] and National Institute for Health and Care Research (NIHR) payment guidance for members of the public considering involvement in research [41].

### Key NHS partners

Key NHS partners in the local health and care system such as clinical managers or commissioners will be identified with the support of the local collaborators.

### Intervention

“Encompass” is a 10-module facilitated, group participatory programme for parents/carers of children with complex neurodisability under the age of 5 years (Fig. 2).

**Fig. 2 Fig2:**
[figure not shown]
The “Encompass” programme modules

“Encompass” aims to run 10 group modules which will follow the topics in Fig. 2. All sessions will be run in person at a community venue such as the local library meeting room. The aim is to run modules fortnightly. Groups will be facilitated by two people: a healthcare professional and an “expert parent”. Facilitators will undergo 3–5 days of training with a master facilitator of the original “Baby Ubuntu” programme.

Families will be invited to the groups from the point at which their child is diagnosed and up to the age of 5 years at the time of enrolment. Siblings will be invited to the “Play and Stimulation” sessions, and any other carers or family/community members will be invited to the “Our Community” session. Handouts will be provided at the end of each group. Group rules/contract will be discussed developed together at the initial group with the assistance of the facilitators.

### Outcomes

#### Primary outcomes

Feasibility, acceptability and process outcome measures will be used. Quantitative data will be collected to assess the traffic light criteria (Table 2). The green light signifies that criteria for progression have been met and a larger evaluation could proceed, the amber light suggests certain amendments need to be made and the red light indicates that the criteria for progression have not been met and researchers should not continue to a trial [42]. The criteria for progression will be collected using the following:Study record: An enrolment log will record all eligible participants, total enrolled, reasons for non-participation, number followed up on the individual-level outcomes and the date on how many people responded to adverts/invitations. Reasons will be recorded for those who are eligible but decline to enrol.Process measurements: Fidelity checklist and qualitative observations of the intervention groups, group register and post-intervention survey from parent/carer participants. The survey has been adapted from previous evaluations of Ubuntu interventions and is scored on a Likert scale for satisfaction with the content, organisation and facilitators.Qualitative data: Semi-structured interviews conducted with parent/carer participants, facilitators and wider key NHS partners (e.g. NHS service managers and commissioners) to explore the acceptability of the intervention.

**Table 2 Tab2:** Traffic light criteria for the larger scale evaluation

	**Green light**	**Amber light**	**Red light**
**Recruitment — percentage of eligible participants who consent to take part**	35% who are eligible consent to participate	15–34% who are eligible consent to participate	Less than 15% who are eligible consent to participate
**Group attendance**	More than 80% of parents/carers attend the group for 6 + sessions	30–79% of parents/carers attend the group for 6 + sessions	Fewer than 30% attend the group for 6 + sessions
**Follow-up response rate — self-complete outcomes questionnaire(s)**	70% or greater response to follow up	50–69% response to follow-up	Less than 50% response to follow-up
**Fidelity — delivery on items described in the fidelity checklist**	70% or greater score on the checklist	50–69% score on the checklist	Less than 50% score on the checklist

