**Methods and analysis:**

We will conduct a mixed-methods pilot feasibility study to determine the feasibility and acceptability of delivering and evaluating “Encompass” with parents/carers of children under 5 years with complex neurodisability in the UK. We aim to recruit 20 parents/carers of children from two NHS trusts in England serving urban areas where there is high social deprivation and ethnic diversity. Recruited parents/carers will attend the 10-modular, participatory group programme over a 6-month period. Groups will be facilitated by a trained allied health professional and an “expert parent” with lived experience. The primary outcomes of interest are the feasibility of delivering and evaluating the programme (recruitment, retention rates, acceptability as perceived by the parents/carers, facilitators and wider key NHS partners), intervention fidelity and participant adherence. Results will be collectively assessed against traffic light criteria. Pre-, post- and follow-up data collection questionnaires will include the Family Empowerment Scale (FES), the Power Ladder Question, the Parent Patient Activation Measure (P-PAM), Warwick-Edinburgh Mental Wellbeing Scale (WEMWBS), EuroQoL-5D-5-level (EQ-5D-5L) and parent/carer greatest needs and goals questionnaire. Post-intervention semi-structured interviews will be conducted with parents/carers, facilitators and key NHS partners.

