### Sample size

The sample size of the study was generated based on a variety of literature and methods. Simple confidence interval calculations were used for the feasibility estimates research questions and qualitative justifications for the acceptability research questions.

As the objectives of the feasibility study relate to estimating a rate (i.e. the proportion of people) of those who completed follow-up questionnaires and attended the groups, it is suggested that confidence intervals may be calculated by relating the proposed sample size to the width of the confidence interval for the rate, using the following equation with *P* being the proportion one expects to see and *n* the intended sample size [58]:$$1.96 \times \surd (P \times (1-P)/n)$$

The standard error of a proportion depends on the value of the proportion itself, reaching its largest value when the proportion equals 0.50 [58]. The table below displays the width of confidence intervals across reference sample sizes for two values of proportion (Table 4):An estimation of the follow-up response rate questionnaires being 70%As estimation of group attendance (attending > 6 out of 10 modules) of 80%

**Table 4 Tab4:** Width of confidence intervals across reference sample sizes for two values of proportion (completion of follow-up questionnaires and group attendance)

*n*	Group configuration		*P*	CI_95_
12	Two groups of six each	Follow-up	0.70	0.26
		Attendance	0.80	0.23
16	Two groups of eight each	Follow-up	0.70	0.22
		Attendance	0.80	0.20
20	Two groups of 10 each or 3 groups of 6 or 7 each	Follow-up	0.70	0.20
		Attendance	0.80	0.18
24	Three groups of eight each	Follow-up	0.70	0.18
		Attendance	0.80	0.16
30	Three groups of 10 each	Follow-up	0.70	0.16
		Attendance	0.80	0.14

For a follow-up response rate of 70% in the feasibility study of 12 participants, we can be 95% confident that this estimate is accurate within + / − 26%. When the sample size is increased to 20 participants, the error in estimation is reduced to 20 percentage points. If increased to 24 participants, this is only slightly reduced to + / − 18%. An increase to 30 participants results in a marginal reduction to + / − 16%.

The above calculations relate to the feasibility rate estimates and suggest that a sample of 20 may be adequate.

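### The attendance row of the traffic-light table gives no colour to exactly 80%, which is 16 of the planned 20 parents/carers and the attendance rate assumed for the sample size

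*Protocol article*

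**What the plan says.** Table 2, under Primary outcomes, sets the three lights for group attendance:

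- green: "More than 80% of parents/carers attend the group for 6 + sessions"
- amber: "30–79% of parents/carers attend the group for 6 + sessions"
- red: "Fewer than 30% attend the group for 6 + sessions"

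The follow-up row of the same table has an inclusive green edge, "70% or greater response to follow up", and the fidelity row is worded in the same way. The recruitment row gives green as "35% who are eligible consent to participate", with nothing to show that higher values count too.

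The Abstract gives the target: "We aim to recruit 20 parents/carers of children from two NHS trusts in England". The Sample size section takes as its planning value "As estimation of group attendance (attending > 6 out of 10 modules) of 80" per cent, and says that its calculations "suggest that a sample of 20 may be adequate". The Data analysis section confirms that attendance will be judged against Table 2. The article gives no rule for ties and no rule for rounding.

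**The concern.** Progression criteria are useful because they are fixed before the result is known. Here the strict green edge and the amber ceiling of 79% leave out one whole-number percentage. With 20 participants, attendance moves in steps of five points, so 80% is a result that can occur. It is also the rate the authors plan for. If the study performs exactly as planned on attendance, the table gives no light, and someone would have to choose the colour after seeing the count. Attendance is one of four quantitative criteria among the primary outcomes.

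**Working it through.** **Inputs.** Bands from Table 2: green above 80%, amber 30–79%, red below 30%. Sample size n = 20 (Abstract and Sample size). Planning rate P = 0.80 (Sample size).

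**1. The plan's own figure.** The half-width for attendance is 1.96 × √(P(1 − P)/n) = 1.96 × √(0.80 × 0.20/20) = 0.1753, which rounds to the 0.18 in Table 4. The other nine entries of Table 4 also reproduce. The inputs are therefore read as the authors meant them.

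**2. Which counts get a colour at n = 20.**

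| Attending 6 or more sessions | Per cent | Light as written |
|---|---|---|
| 0–5 | 0–25 | red |
| 6–15 | 30–75 | amber |
| 16 | 80 | none |
| 17–20 | 85–100 | green |

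Sixteen is the only count in the gap. Rounding cannot rescue it, because 80% is already a whole number.

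**3. How often the gap is hit.** Assume that X, the number attending, is Binomial(20, 0.80), which means independent attendance.

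- P(X = 16) = 4845 × 0.80^16 × 0.20^4 = 0.218. The neighbouring counts have P(15) = 0.175 and P(17) = 0.205, so 16 is the mode.
- P(green, X ≥ 17) = 0.411.
- P(amber, 6 ≤ X ≤ 15) = 0.370.
- P(red, X ≤ 5) is below 0.00001.

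**4. Sensitivity to the true rate (n = 20).**

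| True rate | P(X = 16) | Most probable count |
|---|---|---|
| 70% | 0.130 | 14 |
| 75% | 0.190 | 15 |
| 80% | 0.218 | 16 |
| 85% | 0.182 | 17 |
| 90% | 0.090 | 18 |

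**5. Sensitivity to clustering by group.** The article gives no intra-group correlation, so these values are assumptions. For two groups of 10, each beta-binomial with mean 0.80, a correlation of 0.02 gives P(16) = 0.200 with 16 still the mode. A correlation of 0.05 gives P(16) = 0.178 and moves the mode to 17 (0.182).

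**6. Sensitivity to the number enrolled.** Exactly 80% needs n to be a multiple of five. Between 16 and 24 it can occur only at n = 20.

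**7. The two ways to close the gap, at n = 20 and P = 0.80.**

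- 80% counts as green: P(green) = 0.411 + 0.218 = 0.630 (from unrounded terms), amber 0.370.
- 80% counts as amber: P(green) = 0.411, P(amber) = 0.370 + 0.218 = 0.589 (from unrounded terms).

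**The case against.** Several points on the other side hold.

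- **Consequence.** A reader might infer that the gap leaves open whether the larger evaluation goes ahead. The article does not support that. The Abstract says results are assessed against the criteria collectively, and qualitative findings are considered alongside them. Under Primary outcomes only red means not continuing, and the amber/red edge of the attendance row has no gap at a whole percentage. At 16 of 20 the open question is whether amendments are flagged.
- **Other gaps.** A reader might infer that Table 2 has holes throughout. Values such as 20/58 = 34.5%, 19/24 = 79.2% and 9/13 = 69.2% do fall between the printed bands, but at whole-percent reporting they become 34%, 79% and 69%, all amber. At n = 20 the follow-up row cannot produce such a value. The bare 35% for recruitment is a slip whose meaning is clear from the amber band beneath it.
- **Most likely result.** Calling 16 of 20 the most likely result needs n = 20, a true rate of 80% and independent attendance. Even then 78% of the probability lies on other counts.
- **Same quantity?** The Sample size section attaches its 80% to more than six of ten modules, while Table 2 counts six or more. Read literally, 80% on the stricter definition implies at least 80% on the looser one, so the expected Table 2 rate could be higher.
- **Timing.** Whether the edit can still be made before data are seen is not known. Table 1 describes the facilitators in the past tense, so sessions may already have run.

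None of this gives 80% a colour. It limits how much depends on the gap.

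**Conclusion.** The point holds for the attendance row: exactly 80% has no light, and 16 of the planned 20 is exactly 80%. The chance of landing there is about 0.22 under the planning assumptions, and 0.18 to 0.19 if the true rate is 75% or 85%, or if there is modest clustering within groups. It is zero if the number enrolled is not a multiple of five. What is lost is a pre-stated answer to green versus amber on one of four jointly judged criteria. The way the gap is closed also matters, since it moves the chance of green at the planned rate between 0.41 and 0.63; that is a reason to settle it in writing and not after the count is known. This is a correction that should be made, but not a flaw that undermines the study.

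**What to change.** Rewrite the attendance row of Table 2 so that the bands touch and 80% has one stated colour. One form is green at 80% or more, amber from 30% to below 80%, red below 30%; it follows the inclusive wording of the follow-up and fidelity rows. At n = 20 that is 16–20 green, 6–15 amber, 0–5 red. The alternative keeps green strictly above 80% and extends amber to include it: 17–20 green, 6–16 amber, 0–5 red. The authors should state which they intend and print the counts beside the percentages.

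In the same edit:

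- write the recruitment green cell as 35% or more;
- say whether all bands apply to unrounded proportions, with edges that touch, or to whole percents;
- reconcile the attendance definitions in Table 2 (six or more sessions) and the Sample size section (more than six of ten modules).

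The cost is one table and one line of text, with no further data. If attendance has already been seen, date the change and report it as post hoc.
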